### Measures

Multiple measures were collected over the course of the study. Details regarding these measures are described in Table 1.

**Table 1 Tab1:** Assessment measures across participants and time points

Construct	Measure	Brief description	Time points	Participants	Method/procedure
*Proposed mechanisms of change*					
Knowledge	Test of knowledge	39-items developed to assess advocates knowledge of screening, barriers, engagement strategies, and trauma; mixed format of multiple choice and true/false	Pre-training, post-training, follow-up	Victim Advocate	Self-Report via REDCap
	Self-evaluation of knowledge	20-item measure assessing self-perceived knowledge of evidence-based treatment, mental health, screening, trauma, and engagement strategies	Pre-training, post-training, follow-up	Victim Advocate	Self-Report via REDCap
Skills	Fidelity	Items developed for respondents to rate use of engagement skills during a meeting with caregiver	Pre-training, post-training, follow-up	Victim Advocate	Self-Report via REDCap
*Potential moderators*					
Attitudes	Victim Advocate Attitudes	22-items developed to assess respondents’ attitudes towards mental health, screening, trauma, and supervision	Pre-training, post-training, follow-up	Victim Advocate	Self-Report via REDCap
Barriers to treatment	Perceived barriers to treatment	Advocates perceptions of barriers families face when attempting to access evidence-based mental health services	Pre-training, post-training, follow-up	Victim Advocate	Self-Report via REDCap
Ethnic Sensitivity	Ethnic sensitivity inventory: precontact [48]	5-items assessing respondent’s sensitivity to other cultures and ethnicities	Pre-training, post-training, follow-up	Victim Advocate	Self-Report via REDCap
Organizational support	Perceived organizational support [49]	16 items assessing respondents’ perceptions of the support they receive from their agency	Pre-training, post-training, follow-up	Victim Advocate	Self-Report via REDCap
Supervisory support	Perceived supervisory support [50]	16 items assessing respondents’ perceptions of the support they receive from their supervisor	Pre-training, post-training, follow-up	Victim Advocate	Self-Report via REDCap
Self-Efficacy	General self-efficacy [51]	8-item measure assessing belief in one’s capability to meet task demands across contexts (i.e., self-efficacy)	Pre-training, post-training	Victim Advocate	Self-Report via REDCap
Executive functioning	Behavior Rating Inventory of Executive Function-Adult [52]	Assessment of executive functioning abilities (abbreviated version)	Pre-training	Victim Advocate	Self-Report via REDCap
Learning anxiety	Learner Anxiety Assessment	3-item measure assessing concerns regarding learning new information	Pre-training	Victim Advocate	Self-Report via REDCap
Motivation to learn	Motivation to learn —general [adapted from [53, 54]	3 items assessing trait-like motivation to learn new things	Pre-training	Victim Advocate	Self-Report via REDCap
	Motivation to learn —specific [adapted from [53, 54]	5-items assessing motivation to learn information specific to the E3 training	Pre-training	Victim Advocate	Self-Report via REDCap
*Training evaluation*					
Webinar evaluation	Post-webinar evaluation	Brief measure assessing satisfaction with each webinar and feedback regarding potential improvements	Completed after each webinar	Victim Advocate	Self-Report via REDCap
Overall training evaluation	Post-training evaluation	Measure assessing overall satisfaction with, acceptability of, and feedback regarding E3 training, including webinars, consult calls (when applicable), and related assignments	Post-training	Victim Advocate	Self-Report via REDCap
				Senior Leader	
*Participant and agency characteristics*					
Demographics	Demographic Questionnaire	Basic demographic information	Pre-training, post-training, follow-up	Victim Advocate	Self-Report via REDCap
				Senior Leader	
CAC agency level	Agency Level Questionnaire	Information specific to the CAC, including annual numbers of forensic interviews, funding structure, etc.	Pre-training, post-training, follow-up	Senior Leader	Self-Report via REDCap
	NCA Census	Survey completed by CACs every other year assessing funding sources, staffing information, and detailed information on mental health services provided by CACs and partner agencies	2020	Senior Leader	NCA Census Survey (Qualtrics)
Multidisciplinary team	OMS MDT Biannual Survey	Anonymous, voluntary survey completed by members of the MDT regarding the functioning of MDT, feedback on the process, and suggestions for improving the MDT	Twice yearly survey	MDT members	OMS MDT Survey
*Outcomes*					
CAC Outcome data	Child Contact Data	Basic demographic information about the child, details regarding who met with the family, what was provided during the visit, and whether the family was (1) referred to and (2) subsequently attended a mental health appointment.	Pre-training, post-training, follow-up	Victim Advocate	REDCap
	OMS Initial Caregiver Survey	Anonymous, voluntary survey typically collected on-site at the end of the CAC visit via paper surveys or electronically; obtains family feedback regarding their visit and the support and follow-up provided by CAC staff	Throughout the year, as per CAC protocol	Caregiver report	OMS Initial Caregiver Survey
	OMS Follow-up Caregiver Survey	Anonymous, voluntary survey typically completed via a phone call 4 to 8 weeks post-visit; collects additional feedback regarding on-site visit, support, and subsequent follow-up by CAC and MDT staff	Throughout the year, as per CAC protocol	Caregiver report	OMS Follow-up Caregiver Survey
*Screening*					
Mental health screening	Child Behavioral Health Screener	Pediatric Symptom Checklist (PSC-17 [55];) plus 3 items focused on clinical-level child trauma symptoms, 6 items assessing functional impairment, and 3 critical items assessing suicidality, problematic sexual behavior, and substance use.	Pre-training, post-training, follow-up	Caregiver report (total score)	REDCap

#### Proposed mechanisms of change

The key mechanisms proposed to impact rates of child mental health screening, referral, and linkage to EBP via E3 training are changes in Victim Advocates’ *knowledge* and family engagement *skills*.

A self-report knowledge test directly examined the knowledge Victim Advocates gain through the training process. Items developed focused on engagement strategies, trauma and effects of trauma, evidence-based mental health treatments, screening for child mental health concerns, and strategies for identifying EBP in their own communities. Our goal was to test change in knowledge acquisition by Victim Advocates.

Skill (i.e., fidelity) measures were adapted from previous research examining self-reported fidelity to the TIES model [56], as well as current coding manuals for MI fidelity [57, 58] to create a self-report checklist of skills taught in the training. In consultation with the TIES experts, we developed a self-report checklist that includes both engagement-consistent behaviors (e.g., inquiring about previous mental health experiences) as well as behaviors counter to the MI and TIES strategies (e.g., providing unsolicited advice). The inclusion of both item types ideally decreased the demand for overly positive responses by Victim Advocates. Such a measure will allow us to examine skill development and its influence on primary outcomes (see below).

#### Clinical trial outcomes

Targeted outcomes are as follows: implementation of screening, referrals for services, successful linkage to at least one mental health appointment, types of services accessed (i.e., EBP status), and reduced caregiver stress. These were captured via both OMS caregiver surveys and through REDCap surveys completed by the Victim Advocate to address (a) screening forms implemented, (b) engagement strategies used, (c) results of screening, (d) referrals made, and (e) first treatment session documented by date.

#### Feasibility outcomes

As a pilot study, we included multiple measures of feasibility. Specifically, we developed training evaluation forms to be completed by Victim Advocates immediately after each webinar to determine didactic training acceptability. We implemented an overall training evaluation form, completed by both the training groups at the post-training data collection wave. The overall evaluation measured Victim Advocate and Senior Leader satisfaction with E3 training, their perceptions of the acceptability of the training method for their CAC, and any feedback they had regarding improving the training process in the future. These results, in conjunction with observations of rates of successful data completion and attendance at required training activities, will be examined when determining whether the E3 training is feasible for CACs and any necessary adjustments for future trials. Examination of the feasibility of the study methods was planned through evaluation of the success of data collection completion and cleanliness, as well as feedback from and support provided to the Victim Advocates and Senior Leaders addressing data collection procedures.

#### Moderators

Victim Advocates will approach the training with varying levels of goals, motivations, learning styles, and preferences. In addition, characteristics of the CAC may impact the uptake of the training. As such, surveys of the Victim Advocate and the CAC Director were designed to capture these potential moderators of outcomes. The Victim Advocates completed surveys addressing attitudes, motivation to learn, learning anxiety, ethnic sensitivity, organizational and supervisory support, and barriers to services (see Table 1), while CAC Directors provided descriptive data of the CAC personnel and activities.

#### Costs

To capture direct and indirect costs associated with implementing the E3 training, during the project we tracked (a) the amount of time Victim Advocates spend completing the webinar and pre-work activities, (b) the number and length of consultation calls attended by each Victim Advocate (if applicable), and (c) the number of screening assessments and referrals completed at each CAC. The detailed cost information was collected at the follow-up, comprising of questions about salary/wages and benefits, time, and resource use. Costs associated with the development of the training materials and resources were also collected from the E3 training team to examine overall training development costs.

### Randomization

Prior to study implementation, a power analysis was conducted to determine how many sites would be needed per randomized condition. Because we had three treatment conditions (i.e., E3w, E3w+c, delayed waitlist control), we planned to assess intervention effects for all three two-way combinations of interventions. The power analyses were conducted for each of these two-way comparisons. To avoid overestimating power [59], we used the smallest number of clusters in an intervention group to estimate power. Power analyses were conducted using the Optimal Design software [60]. With a small intraclass correlation (*ρ*=0.05) and 50 total CACs (i.e., total clusters across a pair of intervention conditions), the minimal detectable effect size (MDE) is relatively small *δ*=0.19 as a standardized mean difference assuming 80% power and a type I error rate of 5%. This also assumes there are at least 200 referrals per CAC. For the same design criteria and a larger intraclass correlation (*ρ*=0.50), the MDE is large at 0.57. Overall, power analyses suggested that we randomize at least 25 CACs per condition. We received 114 applications, all of which were evaluated for inclusion criteria. In addition, the research team determined if the CAC lacked the capacity to participate in the training (e.g., only one part-time advocate employed, ongoing participation in multiple training initiatives), they were not included in the randomization. After review, 81 sites were eligible to participate, and all were randomized.

The adaptive randomization process began with a preliminary exploration of baseline covariates that were correlated with the outcome variable caregiver engagement. Variables were taken from pre-existing data collected through the NCA Census (*N* = 753, *q*^1^ = 222), NCA statistical data [*N* = 838, *q* = 68], OMS Surveys (including the caregiver follow-up survey [*N* = 490, *q* = 16] and MDT survey [*N* = 560, *q* = 14]), and pre-RCT surveys (CAC director survey [*N* = 540, *q* = 123] and advocate survey [*N* = 880, *q* = 156]).

Based on factors hypothesized to influence the outcome of interest (i.e., child engagement in EBP), the initial analysis included the following variables: (a) type of location (urban vs. rural), (b) region of the CAC (e.g., Northeast, Southern), (c) number of children served, (g) number of total CAC staff, (d) number of advocates on staff, (e) organization type (e.g., hospital-based, government-based), (f) EBP services provided onsite or via community, (h) level of MDT collaboration, (i) number of barriers CAC staff report experiencing when referring families to EBP, (j) use of a mental health screening tool, (k) advocates previous training experiences, (l) number of children reported to EBP, and (m) number of children who received EBP. The main purpose of the exploratory analysis was to specify the factors most predictive and apply them as the baseline covariates. Both variables (l) and (m) were used as outcomes, and the rest of the variables were predictors in generalized linear models. Because of the exploratory nature of this aim, as well as the existence of missing data, the major risk was a false discovery due to capitalizing on chance. Therefore, the analysis practiced the stepwise model selection based on multiple imputed data [61]. Notably, variables (a) region of the CAC, (b) number of barriers when referring families to EBP, and (c) use of mental health screen tools appeared in more than 50% of the selected models from twenty imputed data. Therefore, this analysis used these three variables as the covariates in the adaptive randomization.

Covariate adaptive randomization is an approach to ensure that the participants are approximately balanced with respect to covariates in the randomization [62]. The current analysis utilized the method of permuted block randomization with eight strata (4 region areas × 2 screen tool usage levels) to assign 81 CAC sites randomly into three arms. Group A (*N* = 26), Group B (*N* = 28), and Group C (*N* = 27), corresponding to E3w, E3w+c, and delayed control, respectively. A preliminary baseline equivalence test was also applied to check whether any differences between the three arms existed. It did not find any difference between groups on children’s rate of referral to EBP (*F*_(2, 78)_ = 0.185, *p* = 0.832), rate of EBP receipt (*F*_(2, 78)_ = 0.146, *p* = 0.864), or number of advocates on staff (*F*_(2, 78)_ = 1.423, *p* = 0.247).

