## Methods/design

### Study design overview

For this randomized controlled trial (RCT), we are testing the feasibility, outcomes, and cost of the two levels of E3 training compared to current practices in CACs in a 1:1:1 allocation ratio. The protocol is to randomize the CACs to the E3w, E3w+c, or a delayed waitlist control condition, with data collected directly from training participants pre-training, immediately post-training, and at follow-up. Further, the protocol is designed to utilize NCA’s standard data systems to collect outcome data from caregivers and community stakeholders pre- and post-training. We hypothesized that the E3 training would be readily implemented within the training structure of NCA and that Victim Advocates and CAC Directors would report high levels of satisfaction with the training. More importantly, we hypothesized that E3w alone would improve Victim Advocates’ knowledge, resulting in a minor improvement in EBP engagement, while the addition of consultation in E3w+c would lead to increased use of engagement skills, thereby resulting in greater improvement in family engagement in EBP (see Fig. 1 for flow diagram). For purposes of the current study, we will examine family engagement via rates of mental health screening, rates of referral to EBP by Victim Advocates, and family attendance at the first session. Cost data was included in the protocol to examine cost-effectiveness in future studies.

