##### Pre-RCT survey

In the first year of the project, prior to the selection and randomization of sites, we implemented an electronic survey of Victim Advocates and Senior Leaders across all CACs. Collected through NCA’s Qualtrics system, the survey was distributed to the national network of CACs. Questions focused on the current roles, responsibilities, activities, tools, and management of Victim Advocates. We received responses from 915 Victim Advocates and 540 CAC Directors, which were then utilized by the training team to develop the E3 training. In addition, several items on mental health screening procedures and barriers that Victim Advocates face when engaging families in EBP were used in the adaptive randomization procedure (see below).

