#### Quantitative analytic plan

The outcomes analysis will be conducted from the post-training and follow-up assessments of Victim Advocates and Senior Leaders, as well as the continual collection of OMS survey data from caregivers and team members. The variables collected from Victim Advocates and Senior Leaders are the time-varying and CAC-varying *provider fidelity*, *knowledge*, and *perceptions* of the utility of training. In addition, outcomes will include *family engagement*. Statistical analysis will include, but is not limited to, the following: (a) applying linear mixed-effect models to evaluate the changes of the primary outcomes between conditions across time, should the distribution of the outcomes and residuals suggest being appropriate [63, 64]; and (b) investigating the mechanism that is responsible for the causal effect between training conditions and outcomes, with the mediator of knowledge/skill achievement. Covariates collected (e.g., perceived supervisory support, learning anxiety) will also be examined for their influence on the outcome of interest. As a feasibility study, the principal goal at this stage is to conduct an initial examination of training implementation and whether the Victim Advocate knowledge and skills change due to training, what factors might be associated with the change, and how that influences family engagement in mental health services. Further, descriptive statistics will be calculated to examine Victim Advocates ratings of acceptability and satisfaction with the training, as well as rates of attendance in training and consultation.

Missing data will not be avoidable due to the large amount of data collected from sites across the nation, and the repeated measurements across multiple time points. We will examine rates of missing data, as well as data cleanliness, to determine Victim Advocates abilities to complete data submission successfully. Further, stochastic multiple imputation methods will be used to handle missingness, if the assumption of ignorable missing mechanism can be held [65, 66]. In addition, analyses will be “intent-to-treat,” such that individual participants or sites who leave the study will be included in analyses.

All the analysis will be completed by the statistical package R (3.5.2) [67] with multiple packages, such as the dplyr, tidyr, ggplot2, lme4, stats, readr, and mice.

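### The article says three covariates entered the randomisation, but the strata it describes use only two; the number of referral barriers is not balanced by that scheme, and adjustment for it is not committed to

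*Protocol article*

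**What the plan says.** The design overview gives cluster randomisation of CACs "in a 1:1:1 allocation ratio". The Randomization section reports: "After review, 81 sites were eligible to participate, and all were randomized". The arms hold 26 (E3w), 28 (E3w+c) and 27 (delayed control) sites.

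The same section describes a stepwise search, over twenty imputed data sets, for predictors of EBP referral and receipt. It kept "variables (a) region of the CAC, (b) number of barriers when referring families to EBP, and (c) use of mental health screen tools", each present in more than half of the selected models, and concludes: "Therefore, this analysis used these three variables as the covariates in the adaptive randomization". The next paragraph describes the allocation as "permuted block randomization with eight strata (4 region areas × 2 screen tool usage levels". The baseline comparison reported after it covers referral rate, EBP receipt rate and number of advocates.

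The Pre-RCT survey section says that items on "barriers that Victim Advocates face when engaging families in EBP were used in the adaptive randomization procedure".

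The Quantitative analytic plan opens: "The outcomes analysis will be conducted from the post-training and follow-up assessments of Victim Advocates and Senior Leaders". It then lists, without claiming to be complete, linear mixed models for change between conditions over time and a mediation analysis. It adds that collected covariates will be examined, with supervisory support and learning anxiety as examples.

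**The concern.** The allocation scheme tells a reader which variables are balanced by design and which the analysis should condition on. Here the article gives two incompatible accounts of it. Under one, barriers was balanced; under the other, it was left to chance. The authors' own search kept only three variables and barriers is one of them, so a reader would take its balance as secured when the described design does not secure it.

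The analysis section does not settle the matter, because it names none of the three as a model term. At stake are a correct account of the allocation and some precision in a trial with 26 to 28 sites per arm.

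**Working it through.** **1. Count the strata.** Region (4 levels) × screening tool (2 levels) = 8, the number stated. Adding barriers as a two-level factor would give 4 × 2 × 2 = 16 strata, with 81/16 ≈ 5 sites each instead of 81/8 ≈ 10. So barriers is not a stratifier in the scheme described. The arm sizes add up: 26 + 28 + 27 = 81.

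**2. Check what the plan's other figures depend on.** The article's minimal detectable effects follow from (t₀.₉₇₅,₄₈ + t₀.₈₀,₄₈) × √[4(ρ + (1−ρ)/n)/J] with J = 50 CACs and n = 200 referrals:
- ρ = 0.05: 2.860 × √(4 × 0.05475/50) = 0.189 (stated 0.19)
- ρ = 0.50: 2.860 × √(4 × 0.5025/50) = 0.573 (stated 0.57)

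Both reproduce with no covariate term, so this point changes no sample size.

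**3. Chance imbalance in barriers.** For a standardised covariate outside the strata, the SD of the difference between two arms is √(1/26 + 1/27) = 0.275. The 95% range is ±1.96 × 0.275 = ±0.54 SD. By the normal approximation, the chance of an absolute difference above 0.25 SD is 36%, and above 0.5 SD it is 7%. The other two arm pairs give nearly the same SD (0.272 and 0.270).

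**4. Effect of leaving the two stratifiers out of the model.** Let R² be the share of site-level variance that they explain. The documents give no figure, so 10, 20 and 30% are assumptions. The true type I error of a nominal 5% two-sided test is 2[1 − Φ(1.96/√(1−R²))] = 3.9, 2.8 and 1.9%.

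A null simulation agrees. It used 8,000 runs per scenario, 81 sites, 8 strata and a site-level linear model. Blocks of 3 and equally likely strata were assumed. Strata and barriers were given the variance shares shown.

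| Strata / barriers share | Type I error, unadjusted | Mean SE vs true SD, unadjusted | Type I error, adjusted for all three |
|---|---|---|---|
| 10% / 5% | 3.8% | 0.271 vs 0.256 | 4.9% |
| 20% / 10% | 3.0% | 0.272 vs 0.244 | 5.0% |
| 30% / 20% | 2.3% | 0.272 vs 0.233 | 5.5% |

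The estimates were unbiased in every scenario.

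**5. Effect of leaving out barriers alone.** With strata at 0% and barriers at 20% of variance, the unadjusted SE is right (0.272 against a true SD of 0.269; type I error 4.8%). Adjusting lowers the SE to 0.245, about 10%. The loss is one of precision only.

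**6. Dilution when clusters are small.** Step 4 treats all variance as site-level. For advocate outcomes, assume 3 advocates per CAC. The between-site share of the variance of a site mean is ρ/(ρ + (1−ρ)/3): 0.05/0.367 = 14% at ρ = 0.05, and 0.50/0.667 = 75% at ρ = 0.50. If the strata explain 10 to 30% of the between-site part, SE inflation 1/√(1−R²) − 1 is about 0.7 to 2% in the first case and 4 to 14% in the second.

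**The case against.** The contradiction about the allocation is not in serious dispute. The case against going further is strong, and most of it stands.

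- **The analysis.** A reader might infer that the analysis adjusts for none of the three variables. The article does not say so. Its list of methods is open, it says covariates will be examined, and a condensed article commonly leaves model terms to an analysis plan, which is not shown here. What can be said is that it makes no commitment.
- **Baseline values.** The opening sentence of the analytic plan might suggest that pre-training data are dropped. The next step models change across time, and Table 1 lists a pre-training wave for knowledge and skills. The documents do not show that baseline is left out.
- **Standard errors.** It is tempting to call them wrong. Leaving out the stratifiers makes them too large, which is conservative; leaving out barriers leaves them valid. In a balanced condition-by-time contrast with site random effects, time-constant site effects cancel, so the figures for the stratifiers would not apply there.
- **Importance of barriers.** The search was exploratory, and the article itself names false discovery as its main risk. The arms are similar on baseline referral and receipt (F = 0.185 and 0.146), the outcomes that barriers was chosen to predict. This is some reassurance, but it does not show that barriers is balanced.
- **The Pre-RCT survey sentence.** It can be read as covering the exploratory step, with which the randomisation process is said to begin. So it needs clarifying and is not clearly an error. The sentence in the Randomization section has no such reading, because it names all three as covariates in the randomisation itself.

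**Conclusion.** The point holds as a misstatement about the allocation: three covariates are claimed and the described strata use two. Barriers is therefore balanced only in expectation, with a chance arm difference of SD about 0.27 SD, and no reported check covers it.

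The consequence for analysis is conditional. If region and screening-tool use are left out of the between-arm models, type I error falls to about 4, 3 or 2% under assumed site-level variance shares of 10, 20 or 30%. The shortfall is smaller where between-site variance is a small part of the total. Leaving out barriers costs precision and nothing else. Neither omission causes bias on average or excess false positives. The variance shares, the block size and the 3 advocates per site are assumptions, because the article gives none of them.

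This is worth correcting while analysis is still reported as ongoing, but the trial's validity does not depend on it.

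**What to change.** 1. State whether and how the number of barriers entered the allocation, and correct the Randomization section to match. Do not simply delete one of the two statements, since the text does not show which is right. Clarify the Pre-RCT survey sentence in the same way.
2. Report the pre-randomisation number of barriers by arm alongside the existing baseline comparison.
3. Name region, screening-tool use and the pre-randomisation barriers count as fixed effects in the between-arm models, and say explicitly that the pre-training wave of the outcome stays in the model. Use the pre-randomisation count, not the advocates' perceived-barriers scale in Table 1. That scale is also measured after training and is not shown to be the same variable.

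The cost is a few lines of text, about 5 site-level degrees of freedom (3 for region, 1 for screening tool, 1 for barriers), and imputation of some barrier values, since the article acknowledges missing data in the variables used for the selection. No sites or data collection are added.

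### The article says three covariates entered the randomization, but the strata it describes use only two, and the analysis text names none of the three as an adjustment covariate

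*Protocol article*

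**What the plan says.** The Randomization section of the protocol article reports an exploratory model selection on pre-existing data, meant to find the site characteristics most predictive of referral to and receipt of evidence-based practice. Three were chosen in over half of the models fitted to twenty imputed data sets: "Notably, variables (a) region of the CAC, (b) number of barriers when referring families to EBP, and (c) use of mental health screen tools". The article concludes: "Therefore, this analysis used these three variables as the covariates in the adaptive randomization".

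The next paragraph, under the label of covariate adaptive randomization, gives the method as "permuted block randomization with eight strata (4 region areas × 2 screen tool usage levels) to assign 81 CAC sites randomly into three arms". It adds: "A preliminary baseline equivalence test was also applied to check whether any differences between the three arms existed". The results given are for referral rate, receipt rate and number of advocates on staff.

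The Quantitative analytic plan opens its list of methods with "Statistical analysis will include, but is not limited to, the following", and its first item is "applying linear mixed-effect models to evaluate the changes of the primary outcomes between conditions across time". On covariates it says: "Covariates collected (e.g., perceived supervisory support, learning anxiety) will also be examined for their influence on the outcome of interest". Region, screening-tool use and number of barriers are not named there.

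**The concern.** The allocation is described in two ways that cannot both be complete. A reader of the first statement would believe that all three selected predictors were balanced by design. A reader of the second sees only two. The baseline checks do not close the gap: they cover number of advocates, a candidate that the selection did not retain, but not number of barriers, which it did retain.

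The analysis text then leaves open whether any of the three enters the between-arm models. For the two stratifying factors, this bears on whether the standard errors are valid: stratification removes variance from the arm contrast, and a model without the strata does not credit that. For barriers, it bears on precision and on protection against chance imbalance. Existing use of a screening tool also bears directly on one targeted outcome, the implementation of screening.

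**Working it through.** **1. Count the strata.** Region has 4 levels and screening-tool use has 2, so 4 × 2 = 8. This equals the stated number of strata, and no level is left for barriers. Arm sizes agree with the total: 26 + 28 + 27 = 81.

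**2. Reproduce the plan's own figures.** Inputs from the Randomization section are J = 50 sites per pairwise comparison, n = 200 referrals per site, 80% power and 5% type I error (taken as two-sided).

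MDE = (t[0.975, J−2] + t[0.80, J−2]) × √(4(ρ + (1−ρ)/n)/J)

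- ρ = 0.05: 0.189 (stated 0.19)
- ρ = 0.50: 0.573 (stated 0.57)

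Both reproduce with no covariates in the formula, so the stated MDEs are not affected by this point. The baseline F tests on (2, 78) degrees of freedom give p = 0.831, 0.864 and 0.247 (stated 0.832, 0.864 and 0.247), which agree within rounding of F.

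**3. Effect of leaving out the strata, single-time-point contrast.** Suppose the strata explain a share R² of the variance of site means and are balanced across arms. Then model SE / true SD is about 1/√(1−R²), and the true type I error is about 2·P(Z > 1.96/√(1−R²)).

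- R² = 0.10: ratio 1.05, type I error 0.039
- R² = 0.20: ratio 1.12, type I error 0.028
- R² = 0.30: ratio 1.20, type I error 0.019

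A site-level simulation (4,000 replicates, 81 sites, 8 strata, permuted blocks of 3, one pair of arms, no true effect) agrees:

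| Strata / barriers share | Model | SE / true SD | Type I error |
|---|---|---|---|
| 20% / 0% | unadjusted | 1.12 | 0.028 |
| 20% / 0% | strata | 1.01 | 0.050 |
| 20% / 10% | unadjusted | 1.11 | 0.032 |
| 20% / 10% | strata + barriers | 1.01 | 0.050 |
| 30% / 20% | unadjusted | 1.19 | 0.020 |
| 30% / 20% | strata + barriers | 1.01 | 0.048 |
| 0% / 20% | unadjusted | 0.995 | 0.050 |

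Block size, equal expected stratum sizes and all variance shares are assumptions; the article gives none of them.

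**4. Effect of leaving out barriers.** The last row isolates it: the unadjusted standard error is valid. Adding barriers lowers the true SD of the arm contrast from 0.273 to 0.248, a gain in precision only. Mean estimates were about 0 in every analysis, so there is no bias. With 26 and 28 sites, the chance difference between arms in mean barriers has SD √(1/26 + 1/28) = 0.272 site-level SDs. It therefore exceeds 1.96 × 0.272 = 0.53 SD in about 1 randomization in 20.

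**5. The contrast the plan names.** The plan models change across time. Stable site effects cancel in a pre-to-post change. In further simulations the unadjusted type I error was:

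- about 0.024–0.038 for a single time point;
- 0.042–0.049 for a change contrast with fully stable site effects;
- 0.022–0.042 when site effects persist only in part.

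**The case against.** The strongest case on the other side has three parts.

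First, the planned model concerns change over time. If region, tool use and barriers act as stable site effects, they cancel within site. A separate simulation of that case, with strata at 30% and barriers at 10% of between-site variance, gave an unadjusted type I error of 0.052 (ICC 0.05) and 0.056 (ICC 0.50), and adding the covariates slightly raised the true SD (0.0426 to 0.0432 and 0.1084 to 0.1098). This stands on its assumption. It fails where site effects persist only in part, and for any contrast at one time point.

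Second, the analysis list is open, the covariate examples are not exhaustive, and a journal article may leave the fixed effects to an analysis plan that is not shown. This also stands: the article is silent on adjustment and does not exclude it. The advocates' perceived barriers to treatment are collected as a potential moderator, but that is not necessarily the pre-trial barriers count used in the selection.

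Third, this is a feasibility pilot, and any error is in the conservative direction.

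A reader might infer more than the article supports:

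- **That reported standard errors are too large.** None are reported; the analysis is described as ongoing.
- **That the omitted third factor inflates them.** It was not a stratifier in the scheme described, so its omission leaves the standard error valid.
- **That barriers are uncontrolled in a way that biases the comparison.** Randomization still balances them in expectation.
- **That adjustment gains a fixed amount of power.** Simulated gains of about 3 to 9 points at the stated MDE hold only for a single-time-point contrast under the assumed variance shares.

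None of this removes the contradiction about the allocation, which the article states in two ways.

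**Conclusion.** The inconsistency is certain on the face of the text: three covariates are claimed, and the strata described use two. As described, the design does not balance number of barriers, and no check of it is reported.

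The consequence for the analysis is conditional. If the between-arm models omit the strata and the strata predict the analysed outcome, the test is conservative. Type I error is then about 0.02–0.04 for a single-time-point contrast with strata at an assumed 10–30% of between-site variance, and close to nominal for a pure change contrast with fully stable site effects. The article gives no estimate of these shares, and it acknowledges a risk of false discovery in the exploratory selection. Omitting barriers costs precision only.

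This is a minor to moderate point, not one that must be fixed before the trial can be interpreted.

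**What to change.** In the Randomization section, reconcile the two statements. Either say how number of barriers entered the allocation, or say that randomization was stratified by region and screening-tool use only.

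In the Quantitative analytic plan, state that the between-arm outcome models include three site-level covariates: region and baseline screening-tool use, as the randomization strata, and baseline number of barriers, as a selected predictor that was not a stratifier (if the second option applies).

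The cost is wording plus about five degrees of freedom per model as main effects: 3 for region, 1 for tool use and 1 for barriers. The covariates come from pre-randomization site data already used for the selection, and the analysis is still under way.
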